#### · *Inclusion criteria*

60~69 years oldChinese residents living in the communityHave a smart phone with an internet connection at home, existing users of TikTok or have a willingness to download and use TikTok

Individuals with sarcopenia screening questionnaire: Five-item (strength, walking assistance, rising from a chair, stair-climbing, and falls) combined with calf circumference [SARC-CalF] ≥11 [2,32]

Individuals with possible sarcopenia, as defined by low Grip Strength [M:<28 kg, F:<18kg] in accordance with the 2019 Asian working group consensus on diagnosis criteria for sarcopenia [2]Be able to attend the community health center (at their own expense if travel is required) on six occasions for the duration of the studyInformed consent for screening and research

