### Sample size

One arm of 35 eligible participants will be recruited. A sample size of 30 participants after attrition (attrition rate 10%~15%) is normally used for a feasibility study [33,34]. Convenience sampling will be utilized in this research. The target population in the two communities will be divided into four categories based on age (60–65 and 66–69 years) and gender (male and female), to determine if there are differences in the acceptability of the intervention process among subgroups of individuals.

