### Randomization, allocation, and blinding

This study is a one-arm pre-post feasibility study, so randomization and allocation are not required currently. A cluster RCT is planned, so there is no need to evaluate the feasibility of individual randomization. Blinding is not appropriate for this study as there is only one arm, and the intervention contents include health education, which explicitly specifies that this is a course aimed at the prevention of sarcopenia. Therefore, it can be readily distinguished that the exercise strategy in our study is for muscle health and sarcopenia prevention by researchers and participants when the intervention begins.

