### Outcomes

As this is a small feasibility study, the main aim is to assess the feasibility and acceptability of the entire research process, from recruitment to the delivery of the intervention and the use of the outcome measurements. The secondary objectives are to compare standard measures at baseline, seven-week post-intervention, and six-week follow-up for muscle-related outcomes, other body measurements as detailed below, and study adherence to evaluate the potential efficacy of the intervention. The outcome measures will be collected at different time points to identify an appropriate primary outcome and estimate parameters for a sample size calculation for an RCT in the future. Final semi-structured interviews with all participants will be conducted to investigate the viability of the intervention and study procedures in greater detail.

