#### · *Body composition*

Body composition measurement will be conducted using a multi-frequency bioelectrical impedance analyzer device (InBody S10; Biospace, Seoul, Korea) according to the manufacturer’s guidelines. BIA calculates body composition by comparing the conductivity of various tissues based on their distinct biological properties. As a cell approaches an ideal spherical shape, its conductivity decreases, as it is proportional to water content and, more specifically, electrolytes. Since adipose tissue is composed of round-shaped cells and contains relatively little water in comparison to other tissues such as muscle, the conductivity of the body will decrease as body fat increases. In order to conduct a multi-segment frequency analysis, electrodes are set at six precise tactile points of the body. Using six different frequencies (1 kHz, 5 kHz, 50 kHz, 250 kHz, 500 kHz, 1000 kHz), more than 30 impedance measurements are obtained from the right and left arms, trunk, and right and left legs [36]. The following body index parameters will be chosen for analysis in this study: skeletal muscle mass (kg), skeletal mass index (kg/m^2^), upper-extremity skeletal muscle mass (kg), lower-extremity skeletal muscle mass (kg), trunk skeletal muscle mass (kg), body fat (kg), body fat percentage (%), body mass index (kg/m^2^), protein (kg), and bone mineral (kg).

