### Data collection and analysis

The PI, who is qualified and experienced with all of the measurements, will be responsible for data collection. To promote the collection of high-quality data, the PI will double-check the collected data.

As for quantitative data analysis, descriptive statistics will be utilized to summarize the percentage of recruitment, baseline participant characteristics (e.g. age, gender, and educational background), attrition rate, compliance rate, height, weight, etc. 95% confidence intervals (CIs) of mean values will be used to determine the difference of secondary outcomes before and after intervention, such as handgrip strength, skeletal muscle mass, body fat, etc. All statistical analyses will be conducted using SPSS Statistics 27.0 (IBM Corp., Armonk, NY, USA). P Values <0.05 will be interpreted as indicating significance.

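### A P<0.05 significance rule is stated for about 20 uncontrolled before-after comparisons that are meant to gauge efficacy and inform the RCT endpoint; it should be removed

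*Protocol article*

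**What the plan says.** The Data collection and analysis section gives the method for the secondary outcomes: "95% confidence intervals (CIs) of mean values will be used to determine the difference of secondary outcomes before and after intervention". After naming the software it adds: "P Values <0.05 will be interpreted as indicating significance". No test, family of outcomes or exploratory label is attached to that sentence.

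The Outcomes section names baseline, the end of the seven-week intervention and the end of the six-week follow-up as the points to compare, and gives the purpose as gauging potential efficacy. It adds that the measures are collected "to identify an appropriate primary outcome and estimate parameters for a sample size calculation for an RCT in the future".

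On design, the Randomization, allocation, and blinding section says: "This study is a one-arm pre-post feasibility study, so randomization and allocation are not required currently". It also rules blinding out. The Sample size section says "One arm of 35 eligible participants will be recruited" and justifies this by convention: "A sample size of 30 participants after attrition (attrition rate 10%~15%) is normally used for a feasibility study". It gives no effect size, standard deviation or power.

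Grip strength is a secondary outcome and also an entry criterion: "Individuals with possible sarcopenia, as defined by low Grip Strength". Calf circumference is likewise measured as an outcome, and enters selection through the SARC-CalF score.

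**The concern.** A significance threshold answers a question that this study was not designed to ask. Without a comparison group, a before-after P value tests whether the mean changed, not whether the programme changed it. Grip, gait and chair-stand tests are done at baseline and at weeks 4, 7, 10 and 13, so practice can contribute. The measurements are taken by the principal investigator, who knows that everyone is treated. General drift over 13 weeks also counts as change.

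Many outcomes are then read against the same threshold, so some significant changes are to be expected even if nothing changes. What is at stake is how the results are reported and used. A few outcomes labelled significant could be read as evidence of efficacy, and could weigh in the choice of endpoint and assumed effect for the planned cluster RCT. An outcome picked because its change looked large would tend to carry an overstated effect into that trial's sample size.

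**Working it through.** **The plan's own figure.** To keep 30 participants, 30/(1-0.10) = 33.3, so 34; and 30/(1-0.15) = 35.3, so 36. In reverse, 35 x 0.90 = 31.5 and 35 x 0.85 = 29.75. The stated 35 is consistent with its convention. It rests on no test, so removing the significance rule leaves it unchanged.

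**Number of outcomes** (from the outcome subsections and Table 1):
- grip strength: 1
- height, weight, calf and abdominal circumference: 4
- body composition parameters, introduced by "The following body index parameters will be chosen for analysis in this study": 10
- walk test and chair-stand test: 2
- MNA-SF, knowledge quiz, self-efficacy, self-management: 4

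Total 1 + 4 + 10 + 2 + 4 = 21, or 20 without height, which will barely change. Video exposure, the adherence scale and subscales could add a few.

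**Expected false positives with no true change.** 21 x 0.05 = 1.05 per time point. Over weeks 7 and 13, 42 x 0.05 = 2.1. Correlation does not alter these expectations.

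**Chance of at least one, if independent:** 1 - 0.95^k.
- k = 20: 64.2%
- k = 21: 65.9%
- k = 42: 88.4%
- k = 12 (the ten body composition parameters counted as one): 46.0%

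**Allowing for correlation.** Data sets of 30 participants were simulated (6,000 per setting) with 21 normally distributed changes of mean zero, equal pairwise correlation, and a two-sided paired t test at 5%. The protocol does not state the test or its sidedness, so both are assumptions.

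| Correlation | Chance of at least one P<0.05 among 21 |
|---|---|
| 0 | 66% |
| 0.3 | 55% |
| 0.5 | 44% |
| 0.7 | 29% |
| 0.9 | 17% |

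These figures cover chance alone. Practice and drift would add to them.

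**Grip as an entry criterion (conditional).** If the screening value were reused as baseline, the expected spurious gain is (1 - r) x (population mean - mean of those below the cut-off), where r is test-retest reliability. All population values below are assumed.
- Women, mean 22, SD 5, cut-off 18 kg: mean below the cut-off 15.16, gap 6.84; 0.05 x 6.84 = 0.34 kg to 0.20 x 6.84 = 1.37 kg for r from 0.95 to 0.80.
- Men, mean 36, SD 7, cut-off 28 kg: mean below the cut-off 24.52, gap 11.48; 0.57 to 2.30 kg.
- Women, mean 18, SD 5 (a weaker source population): 0.2 to 0.8 kg.

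A simulation with 15 women (mean 22, SD 4.5) and 15 men (mean 34, SD 6.5) and no effect gave a mean gain of 0.4 to 1.6 kg and P<0.05 in about 22% to 69% of studies when the screening value was reused. With a fresh baseline, P<0.05 occurred in about 5%.

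**The case against.** The strongest reply is that the article already leads with confidence intervals, hedges its claims as preliminary or potential, makes feasibility the primary aim, and admits in the Discussion that the single arm is a limitation. No go/no-go decision hangs on P<0.05. A multiplicity method could sit in an unseen analysis plan. All of this is fair, and the absence of a multiplicity adjustment is not the point here. None of it qualifies the significance sentence, which is stated and has no exploratory label.

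A reader might infer three stronger things that the text does not support.

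First, that the RCT endpoint will be chosen by P value. The Outcomes section gives no selection rule, and the primary-aim list already plans to record data collection time and whether participants find the measures tiring or burdensome.

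Second, that 66% or 88% is the realistic chance of a false positive. Those are independence figures. Ten outcomes come from one device, weight and BMI are nearly one variable, and the week 7 and week 13 changes share a baseline.

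Third, that grip is already biased by regression to the mean. Nothing says that the screening value becomes baseline. Eligibility grip is measured before at least 24 hours for consideration, consent precedes data collection, and the six required attendances match the six time points in Table 1. A separate baseline measurement is the more natural reading, though it is not stated outright.

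**Conclusion.** The point holds in a limited form. As written, the protocol labels uncontrolled before-after change as significant across about 20 to 21 outcomes, in a study with no control, no blinding and no powered hypothesis, and gives those comparisons a role in judging potential efficacy and informing the RCT. With no true change, about one outcome per time point would be expected to cross the threshold. The chance of at least one among 21 is at most 66%, and about 55% to 17% at correlations of 0.3 to 0.9, assuming two-sided tests, roughly normal changes and 30 evaluable participants.

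Selection of the RCT endpoint by P value is a risk to guard against, not something the protocol states. The regression-to-the-mean figures of 0.3 to 2.3 kg apply only if the screening grip is reused, and depend on the assumed population values.

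**What to change.** 1. Delete the P<0.05 sentence from Data collection and analysis.
2. Report each secondary outcome as a mean change from baseline with its 95% confidence interval, labelled exploratory, and state that no efficacy conclusion is drawn. The label is needed because an interval that excludes zero can otherwise be read as the same test.
3. State in Outcomes that the RCT primary outcome will be chosen on completeness, floor and ceiling effects, participant burden and measurement variability, and not on P values or size of change.
4. Confirm in one sentence that T0 grip and calf circumference are fresh post-consent measurements and that screening values are not used as baseline.

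The cost is wording. The sample size is unaffected and no outcome is dropped. If T0 is already a separate visit, as the schedule suggests, the last item adds no procedure. The sponsor gives up only the term significant for these comparisons.

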### Data management

The PI will preserve the confidentiality of participants taking part in the study and fulfil transparency requirements under the General Data Protection Regulation for health and care research. Data and all appropriate documentation will be confidentially and securely stored for a minimum of 10 years after the completion of the study, including the follow-up period.

### Study monitoring

The PI will oversee participant recruitment, intervention and follow-up. In addition, one community leader in each cooperative community health center will assume overall responsibility for participant identification and recruitment. One team comprised of research professionals from the United Kingdom and China will be responsible for ensuring the overall quality of research data. All principal researchers will hold a monthly online meeting to report on the project’s progress and discuss its problems and solutions. A thorough risk assessment has been conducted, and potential patient, organizational, and study hazards, as well as their likelihood of occurrence and potential consequences, have been considered.

## Discussion

This research aims to test the feasibility and acceptability of a social-media based multicomponent intervention (health education + exercise) for community young-old adults with possible sarcopenia. Utilizing a mixed-methods approach will enable the investigation of barriers and facilitators to a successful implementation of the intervention, in order to adequately prepare for the future implementation of a randomized controlled trial. Additionally, based on quantitative data analysis, this study will be the first to observe the potential impact of a social-media intervention on the awareness and behavior change of older individuals in preventing sarcopenia, with the ultimate goal of enhancing their muscle performance.

However, there are still some limitations in this research. First of all, the feasibility study was developed as a single-arm pre-post study rather than a feasibility randomized controlled trial due to limited resources (few researchers, limited time and funding). In the future, a multi-center feasibility randomized controlled trial will be considered to explore the feasibility of the research and validate potential effects between different intervention groups, including social media-based health education plus exercise, social media-based health education, social media-based exercise, and control group. Secondly, this study will recruit samples from only two communities, potentially leading to a sample that is not adequately representative. Enhancing the representativeness of future studies can be achieved by expanding the recruitment area. Thirdly, the exercise design failed to incorporate older people who depend on mobility aids such as wheelchairs or crutches. Future studies could explore the creation of customized exercise programs for this specific demographic. Fourthly, this study will exclude older people who do not have Internet access. Therefore, exploring the possibility of integrating both online and offline interventions to prevent sarcopenia is also an innovation area in the future.

The research data and findings of this study will be presented in peer-reviewed journals and scientific conferences, as well as be shared through a series of public engagement events including webinars. The anonymized participant level dataset will not be publicly available but will be available from the PI upon reasonable request.
